### Estimation of the Expected Effect Sizes and Sample Size

The maximal SDS score is 15 points, and the average SDS standard deviation in previous studies was 5 points. As we expect relatively large cocaine consumption differences between participants, we expect a conservative SDS deviation of 7.5 points. For a successful reduction in cocaine use, an average 25% SDS score reduction (3.75 points reduction for a small to medium effect size) is anticipated. This results in a total sample of 25 participants in each group (α = .05, 1-β = 0.8). According to the pilot study, we expect 70% of the participants to quit the study before completion at six weeks. We thus aim to recruit a total of 170 participants at baseline.

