### Measurement instruments

The primary outcome instrument, the Severity of Dependence Scale (SDS), is a 5-item questionnaire that indicates the severity of dependence on cocaine. Each of the five items is scored on a 4-point scale (0-3). The total score is obtained through the addition of the 5 item ratings. High scores indicate a high level of dependency.

Moreover, the following secondary outcome instruments will be applied: 1) The Cocaine Craving Questionnaire Brief CCQ-B [21] is a short (10 items) and validated instrument that was derived from the CCQ-Now [22] (45 items). It contains 10 craving symptoms that are rated on a 7-point Likert scale from strongly agree to strongly disagree. 2) The "Fragebogen Substanzanamnese" (FDA) ascertains the years of lifetime consumption, the past month's consumption, and the way of consumption for the DSM-IV/ICD-10 substances of abuse. This measure was derived from the EuropeASI [23]. 3) The short version of the Beck Depression Inventory (BDI-V) [24] is a derived, validated, and user-friendly short version of the classical Beck Depression Inventory. The BDI-V contains 20 items with a 6-point Likert scale (0/never-1-2-3-4-5/almost every time). Accordingly, the values range from 0 to 100, with a cut-off of 45 for a serious depressive episode that requires further treatment.

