### Consent Procedure

The rationale of the study will be explained to the participants. They will also be informed about the different assessments, assessment schedules and duration. The participants will then be informed about (1) study inclusion and exclusion criteria (see table 1), (2) the potential risks of participation, (3) safety arrangements during and after the study phase, (4) the inability of Snow Control to replace face-to-face therapy for problematic cocaine use/abuse, and (5) the circumstances under which they should contact their general practitioner or a professional from the medical advisory and emergency list that will be accessible at all times and how to make this contact. The participants will also be informed that the study has been reviewed by the ethic committee of the Canton of Zurich and given their declaration of no objection (nihil obstat). Moreover, they will be informed about their right to withdraw from the study at any time without consequences except for the loss of further compensation. Informed consent will be accepted when participants click on a field on the informed consent page and submit the consent with a submission button.

**Table 1 T1:** Inclusion and exclusion criteria and reasoning

*Inclusion Criteria*	Reasoning
- Minimal age of 18 years	To ensure a minimal age of participation
- Cocaine use > 2 occasions in the last 30 days	To include occasional users in order to provide extended study validity
***Exclusion Criteria***	**Reasoning**
- Participation in other psycho-social or pharmacological treatments for the reduction/cessation of cocaine use	To avoid confounding of treatment effects
- Opioid use in the last 30 days (exception: substitution maintenance treatment for opioid dependence without heroin use in the last 30 days)	To avoid confounding of drug effects
- Ever been in treatment for cardiovascular problems or apoplexy	To avoid subjects with these problems entering the study
- BDI-V score > 45	To avoid subjects with serious symptoms of depression entering the study

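### The sample-size inputs do not fit together: SD 7.5 is the ceiling for a 0–15 score, 3.75 points is 25% of the scale maximum with no control-arm change, and 25 per group does not give 80% power

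*Protocol article*

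**What the plan says.** Under Measurement instruments, the protocol article describes the SDS as five items: "Each of the five items is scored on a 4-point scale (0-3" with the ratings summed, so the total runs from 0 to 15.

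The section on expected effect sizes and sample size starts from "The maximal SDS score is 15 points, and the average SDS standard deviation in previous studies was 5 points". It then widens the spread: "As we expect relatively large cocaine consumption differences between participants, we expect a conservative SDS deviation of 7.5 points". The target follows: "an average 25% SDS score reduction (3.75 points reduction for a small to medium effect size) is anticipated". The result is "This results in a total sample of 25 participants in each group (α = .05, 1-β = 0.8". Because "we expect 70% of the participants to quit the study before completion at six weeks", recruitment is set at 170.

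Under Hypotheses, the claim to be tested is that SDS falls further with therapy than with control. The Background describes that control as eight psycho-educative modules with weekly quizzes. Table 1 admits people with more than two occasions of use in 30 days, with the reason "To include occasional users in order to provide extended study validity", and sets no minimum SDS. The article gives no expected baseline mean, no expected control-arm reduction, no between-group difference, no named test and no sidedness for the calculation.

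**The concern.** Three features stand out.

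- The planning SD equals half the scale range, which is the theoretical limit for a bounded score.
- The percentage reduction appears to be taken of the top of the scale, not of where participants will start.
- The reduction has no comparator, although the trial tests a difference between arms.

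The large SD and the large difference partly offset each other and produce a modest-looking d of 0.50. At stake is whether the stated 80% power can be relied on when the result is read, especially a null result.

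**Working it through.** **Inputs.** From the article: SDS range 0–15; previous SD 5; planning SD 7.5; reduction 3.75 points; α = 0.05; power 0.80; 25 per group; 70% loss; 170 recruited. Two-sided testing and an unadjusted t-test are my assumptions.

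**1. The SD.** For a score on 0–15 with mean m, the SD is at most √(m(15 − m)).

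| Mean | Maximum SD |
|---|---|
| 6 | 7.35 |
| 7.5 | 7.50 |
| 8 | 7.48 |
| 10 | 7.07 |
| 12 | 6.00 |
| 15 | 0 |

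An SD of 7.5 therefore requires a mean of exactly 7.5, with half the scores at 0 and half at 15.

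**2. The 25%.** 0.25 × 15 = 3.75. This is an average 25% reduction only if the baseline mean is 15, where the SD is 0. At the mean that an SD of 7.5 requires, 0.25 × 7.5 = 1.875. The two inputs cannot both describe baseline scores.

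**3. The effect-size label.** 3.75 / 7.5 = 0.50, which fits the small-to-medium label. 3.75 / 5 = 0.75, which does not.

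**4. The plan's own figure.** Normal approximation for two groups: n = 2[(1.96 + 0.8416)/d]² per group.

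- d = 0.50: 62.8, so 63 (64 by t-test).
- d = 0.75: 27.9, so 28 (29 by t-test).

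Neither gives 25. One-sided, the t-test needs 51 per group at d = 0.50 and 23 at d = 0.75. A one-sample, one-sided normal formula at d = 0.50 does give 25: [(1.645 + 0.842)/0.5]² = 24.7.

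**5. Power with 25 per group (t-test).**

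| SD | d | Two-sided | One-sided |
|---|---|---|---|
| 7.5 | 0.50 | 41% | 54% |
| 5 | 0.75 | 74% | 83% |

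The smallest d detectable with 80% power, two-sided, is 0.81. That is 0.81 × 5 = 4.0 points at SD 5 and 0.81 × 7.5 = 6.1 points at SD 7.5.

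**6. Dropout.** 50 / 0.30 = 167, rounded to 170; 170 × 0.30 = 51, about 25 per group. This step is sound.

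**7. Illustration only.** The article gives no baseline mean, so those below are assumed, with SD 5, no control-arm change, and a true 25% reduction.

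| Assumed mean | Reduction | d | Power, 25 per group, two-sided | n per group for 80% |
|---|---|---|---|---|
| 6 | 1.5 | 0.30 | 18% | 176 |
| 8 | 2.0 | 0.40 | 28% | 100 |
| 10 | 2.5 | 0.50 | 41% | 64 |
| 12 | 3.0 | 0.60 | 55% | 45 |

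Adjusting for baseline with an assumed correlation of 0.5 divides the SD by 1/√(1 − 0.25) and raises these powers to about 22 / 36 / 52 / 67%. Any improvement in the control arm lowers them.

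**The case against.** **The SD is not impossible, and a large SD is cautious.** Both are true. 7.5 is attainable in a degenerate split, and for a fixed difference it raises the required n: 64 per group against 29 at SD 5. A reader might infer that the SD alone makes the trial too small; it does not. The faults are that 7.5 is not a realistic planning value, that it cannot sit beside the 25% figure, and that the stated n does not follow from it.

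**The ceiling is for scores, and the outcome is a change.** A change score runs from −15 to +15 and can have an SD above 7.5. With SD 5 at both visits and no correlation, it would be √2 × 5 = 7.07. The article does not say which SD it means, but it introduces 7.5 as a widening of an SDS score SD of 5. This objection supports asking which SD is meant; it does not reconcile the inputs.

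**The reduction may be meant as a between-group difference.** A reader might infer from the wording, and from the one-sample formula that returns 25, that the calculation was done within one arm. The article never says so. What the text supports is narrower: the comparison is unspecified and the control-arm change is absent.

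**The analysis could be more efficient than a t-test.** Repeated-measures ANOVA with multiple imputation is planned. At SD 7.5, baseline adjustment reaches about 25 per group only with a correlation near 0.8. At SD 5 and the full 3.75 points, a correlation of about 0.4 would be enough (81% power). So 80% is reachable under some readings, but each needs an SD, a sidedness or a correlation that the sample-size section does not adopt.

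**The SD of 5 has no reference.** This stands. The article attributes it only to previous studies and gives a reason for expecting wider spread. It should not be adopted without justification.

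**Conclusion.** The planning inputs are incoherent on the article's own text, and the stated 80% power does not follow from them. Under a two-sided, unadjusted two-group t-test, the article's d of 0.50 needs about 64 per group against the stated 25, which gives about 41% power. Replacing the SD with 5 and keeping 3.75 points gives 29 per group and 74%. The incoherence of the SD and the percentage, and the missing control-arm change, do not depend on the choice of test; the power figures do.

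A reader might infer that the trial is bound to miss a genuine 25% reduction. The documents do not support that: the 18–55% range rests on assumed baseline means and an unadjusted analysis.

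**What to change.** Rewrite the sample-size paragraph so that it:

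- uses an attainable SD with its source or reason (5 or another value), and says whether it applies to scores or to change;
- gives the target as a between-group difference in SDS change at 6 weeks, with the assumed control-arm change;
- derives any percentage from an expected mean baseline SDS;
- names the test, its sidedness and any baseline correlation used;
- restates d, and the power or detectable difference that 170 recruited (about 25 completers per group) gives;
- removes or corrects the small-to-medium label.

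This changes protocol wording only. Enrolment need not increase. The cost is a stated power that will probably be less favourable than 80%.

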### Handling of study dropouts

Each week, participants will be sent an automated e-mail that contains a reminder to work on the next module and a direct link to the Snow Control login site. If participants do not log in, they will receive a reminder e-mail every three days within the following two weeks. If they do not continue their participation after these reminders, they will be considered to have dropped out of the study. Participants who skip one of the study questionnaires by not answering all of the questions will be identified in the data analyses and counted as dropout (cut-off: answered at least 70% of the questions).

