### Data Analysis

Data will be analysed according to the intention-to-treat principle. Multiple imputations of missing data handling procedures will be implemented using the statistical software package STATA (version 10). Baseline measurements will be compared using t- and Chi-squared tests. Differences between primary and secondary outcome variables at three and six weeks will be tested using a repeated measures ANOVA. Effect sizes will be calculated using Cohen's d [27]. Differences in treatment retention will be tested using multiple logistic regression analyses. We will additionally conduct explorative regression analyses in order to test whether baseline variables predict cocaine abstinence, cocaine craving (CCQ-B), or reduced symptoms of depression (BDI-V). For these analyses, we will use linear, multinomial, or binary regression models dependent on the scale level of the outcome measures.

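### The stated 80% power is not shown for the planned intention-to-treat analysis of 170, and the stated inputs do not give it for 25 completers per group either

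*Protocol article*

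**What the plan says.** All of the sizing is in the protocol article, under Estimation of the Expected Effect Sizes and Sample Size. Earlier studies are summarised as "the average SDS standard deviation in previous studies was 5 points", but the calculation uses a larger value: "we expect a conservative SDS deviation of 7.5 points". The effect is "an average 25% SDS score reduction (3.75 points reduction for a small to medium effect size) is anticipated". The result is "This results in a total sample of 25 participants in each group (α = .05, 1-β = 0.8". The section then expects 70% of participants to leave before six weeks and sets recruitment at 170.

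The Data Analysis section says "Data will be analysed according to the intention-to-treat principle", with multiple imputation and a repeated measures ANOVA at three and six weeks. The Discussion adds that all missing values will be imputed. Under Handling of study dropouts, participants who stop logging in receive reminders, and "If they do not continue their participation after these reminders, they will be considered to have dropped out of the study". That section also counts as dropouts those who answer too little of a questionnaire.

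The Hypotheses section makes the comparison one between groups: a larger SDS reduction on therapy than on control. The article gives no effect for all randomised participants, no effect for those who quit, and no power for the analysis at 170.

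**The concern.** A power statement should describe the analysis that will be run. Here it describes about 25 completers per group with the full 3.75 points, while the written analysis covers everyone randomised, most of whom are expected to have no six-week outcome.

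Dividing by the expected retention restores the number observed. It does not settle what effect is expected in people who stop. In a therapy delivered by login, with modules released week by week, people who stop logging in also stop receiving treatment. The average effect over all randomised participants may therefore be smaller than the effect in those who stay.

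The 80% itself also has to follow from the inputs beside it. If it does not, a non-significant result would be read as evidence against the therapy from a trial believed to have 80% power when its real power was much lower.

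**Working it through.** **Inputs.** From the sample size section: difference 3.75 points (25% of the 15-point maximum), SD 7.5, alpha .05, target power 0.8, 25 per group, 70% quitting, 170 recruited. Sidedness is not stated; I use two-sided and show one-sided beside it. Equal allocation is assumed, so 85 per group. Power is for the two-sample t-test unless noted.

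**Step 1: who the 25 per group are.** 2 × 25 = 50; 50 / (1 − 0.70) = 166.7, so 167, close to 170. In the other direction, 170 × 0.30 = 51, or 25.5 per group. The 25 are the expected six-week completers, and this step is correct.

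**Step 2: does 25 per group follow from the inputs?** d = 3.75 / 7.5 = 0.50. Normal approximation: n per group = 2 × [(1.960 + 0.842) / 0.50]² = 62.8, so 63.

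| SD | d | n per group for 80%, two-sided / one-sided | Power at 25 per group, two-sided / one-sided |
|---|---|---|---|
| 7.5 (plan) | 0.50 | 64 / 51 | 41% / 54% |
| 5 (earlier studies) | 0.75 | 29 / 23 | 74% / 83% |

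No row gives 25. Two other routes come close:
- A one-sample, one-sided formula: [(1.645 + 0.842) × 7.5 / 3.75]² = 24.7, so 25. This tests change within a single group, not the between-group hypothesis.
- A two-group comparison using baseline, with a baseline correlation of about 0.77 to 0.80. With adjustment for baseline, 62.8 × (1 − 0.77²) = 25.6. No correlation is stated.

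**Step 3: intention-to-treat with the full effect in everyone.** Suppose outcomes are missing at random, imputation adds little information, and quitters have the same between-group difference as completers. The analysis then has roughly the information of 25 per group and the 3.75-point effect, so power stays at about 41%. Observed three-week SDS scores could raise this; by how much cannot be computed from the article.

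**Step 4: intention-to-treat with a smaller effect in quitters.** Let f be the share of the 3.75 points kept by quitters. The article gives no value, so the range is 0 to 1. The difference in all randomised participants is 3.75 × (0.3 + 0.7f). The table keeps SD at 7.5 and supposes that all 85 per group are observed, which is the favourable case.

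| f | Difference (points) | d | Power, two-sided |
|---|---|---|---|
| 0 | 3.75 × 0.300 = 1.13 | 0.150 | 16% |
| 0.25 | 3.75 × 0.475 = 1.78 | 0.2375 | 34% |
| 0.5 | 3.75 × 0.650 = 2.44 | 0.325 | 56% |
| 0.75 | 3.75 × 0.825 = 3.09 | 0.4125 | 76% |
| 1 | 3.75 | 0.50 | 90% |

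With 85 per group, 80% power needs d = 0.432, or 3.24 points. Solving 0.3 + 0.7f = 0.432 / 0.50 gives f of about 0.81.

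**Sensitivity to SD.** With SD 5, the figures at f = 0, 0.5 and 1 are 31%, 88% and above 99%. Under that SD the conclusion is milder, but the plan chose 7.5.

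**The case against.** The strongest reply is that powering on expected completers and dividing by (1 − dropout) is ordinary practice. The article speaks of quitting the study, which means missing outcomes. Under missing-at-random imputation, an intention-to-treat analysis keeps the completers' effect with roughly their information. This stands: sizing on completers does not in itself contradict intention-to-treat, and any loss beyond Step 3 depends on how quitters fare.

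The article is also silent on f, and it does not say that the 3.75 points apply to completers only. Its wording is "For a successful reduction in cocaine use, an average 25% SDS score reduction". Quitting need not mean little therapy either: someone who leaves after module 4 has had all the key modules. This stands too, and it is why f appears as a range. A reader might infer from the f = 0 row that the trial has only 16% power. The article does not support that, because nothing in it fixes f at 0.

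A reader might also combine a diluted effect with information from only 25 per group and report still lower power. Ordinary imputation from completers who show the full effect would not produce the diluted difference. That would need a not-at-random model, which the article does not specify.

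The opposite inference is that the 80% is sound for completers and only mislabelled for intention-to-treat. Step 2 rules this out at d = 0.50. Getting 80% from 25 per group would take d of about 0.81, which is not the plan's effect.

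Finally, a full protocol or analysis plan may say more. That excuses missing detail, but not a printed figure that fails to follow from the inputs printed with it.

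**Conclusion.** The point holds in this form. The 80% is not shown for the planned analysis, and the stated inputs do not give it for 25 completers per group either. The part that needs no assumption about quitters is the two-group arithmetic: about 41% power two-sided (54% one-sided), with about 64 per group needed for 80% two-sided. It rests only on an unadjusted comparison with the stated SD; a baseline correlation of about 0.77 or more could rescue the figure, but none is given.

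The intention-to-treat part is conditional. Power is about 41% under missing at random with the full effect in quitters and little gain from imputation. It runs from 16% to 90% over f = 0 to 1 if every outcome were observed. The article does not say where the trial lies in that range, nor does it claim in so many words that the 80% applies to intention-to-treat. The fault is that its only power figure is unsupported by its own inputs and does not address the analysis it plans. This should be corrected, and it does not call the design itself into question.

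**What to change.** Rewrite the sample size paragraph; do not keep the 80% under the label of a completer figure. State the power that N = 170 gives for the planned between-group intention-to-treat analysis, computed from the stated 3.75 points and SD 7.5. State with it:

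- whether the test is one- or two-sided;
- any baseline correlation that is assumed, and its basis;
- the 70% of six-week outcomes expected to be missing, and how much information imputation is assumed to recover;
- the effect expected in all randomised participants, with a short range for f (for example 0, 0.5 and 1). If 3.75 points is meant for everyone randomised, say so and justify it.

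Add one sentence saying that a non-significant result will be interpreted against that power and the confidence interval, not against 80%.

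The cost is one revised paragraph and a small table, with no extra participants. The downside is a less favourable stated power.

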### Hypotheses

We hypothesise that Snow Control participants in the therapy group will show higher reductions on the Severity of Dependence Scale (SDS) [20] sum score and cocaine consumption than those in the control group at the 6-week treatment termination and at the 6-month follow up. Moreover, we expect participants in the therapy group to improve more significantly with respect to the secondary outcomes between baseline and 6-week treatment termination. We also expect the participants in the therapy group to show significantly higher retention.

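### The 25 participants per group do not follow from the plan's own inputs: a two-group comparison needs 64 (two-sided) or 51 (one-sided), and 25 gives about 41% or 54% power instead of 80%

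*Protocol article*

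**What the plan says.** All the inputs are in the protocol article, under Estimation of the Expected Effect Sizes and Sample Size.

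- Spread: "the average SDS standard deviation in previous studies was 5 points", but for planning "we expect a conservative SDS deviation of 7.5 points".
- Effect: "an average 25% SDS score reduction (3.75 points reduction for a small to medium effect size) is anticipated".
- Error rates: "α = .05, 1-β = 0.8", with no statement of one- or two-sided testing.
- Result: "This results in a total sample of 25 participants in each group".
- Recruitment: 70% are expected to leave before six weeks, and so "We thus aim to recruit a total of 170 participants at baseline".

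The comparison to be powered is under Hypotheses: therapy participants "will show higher reductions on the Severity of Dependence Scale (SDS) [20] sum score and cocaine consumption than those in the control group". The Data Analysis section names a repeated measures ANOVA for the three- and six-week outcomes, intention to treat and multiple imputation. Neither section gives a correlation between visits.

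**The concern.** The section prints a complete set of inputs and a result that those inputs do not produce for a comparison of two groups. This is not detail that a journal article leaves to a fuller document, because the inputs and the output stand together in one paragraph and disagree.

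The 25 also sets the size of the trial, since the 170 is derived from it. A reader who trusts the 80% will give a non-significant result more weight against the therapy than the design supports. The Discussion makes integration of the programme into basic services conditional on efficacy being shown, so how such a result is read matters.

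**Working it through.** **Inputs.** Difference 3.75 (25% of the 15-point maximum), SD 7.5, alpha .05, power 0.80, all from the sample-size section. Equal groups are taken from the two-arm design and the single per-group figure. Sidedness is not stated, so both versions are shown.

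**1. Standardised effect.** d = 3.75/7.5 = 0.50. With the historical SD, d = 3.75/5 = 0.75.

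**2. Required size, two independent groups.** Normal approximation: n per group = 2 × (z for alpha + z for power)² / d².

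- Two-sided, d = 0.50: 2 × (1.960 + 0.842)² / 0.25 = 62.8, so 63. The t-test gives 63.8, so 64.
- One-sided, d = 0.50: 2 × (1.645 + 0.842)² / 0.25 = 49.5, so 50. The t-test gives 50.2, so 51.
- d = 0.75, t-test: 28.9, so 29 two-sided; 22.7, so 23 one-sided.

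None of these is 25.

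**3. Attempt to reproduce 25.** A one-sample (before-after), one-sided normal formula gives (1.645 + 0.842)² / 0.25 = 24.7, which rounds up to 25. This is also half of the 49.5 in step 2. No other calculation tried on the stated inputs alone returns 25. It does not test therapy against control, and that the 25 came from it is an inference.

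**4. Power at 25 per group (t-test).**

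| SD | d | two-sided | one-sided |
|---|---|---|---|
| 7.5 | 0.50 | 41% | 54% |
| 5 | 0.75 | 74% | 83% |

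The effect detectable with 80% power, two-sided, is d = 0.81. That is 0.81 × 7.5 = 6.1 points at SD 7.5, or 0.81 × 5 = 4.0 points at SD 5.

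**5. Recruitment step.** 2 × 25 / 0.30 = 166.7, rounded to 170. This step is sound, and it shows that the 25 counts completers. In reverse, 170 × 0.30 = 51 completers, about 25 per group. With 64 per group the same step gives 128/0.30 = 427; with 51 it gives 102/0.30 = 340.

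**6. What an adjusted or repeated-measures analysis would need** (SD 7.5, two-sided, normal approximation).

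- Baseline-adjusted (ANCOVA): 62.8 × (1 − r²) = 25 requires r = 0.78. At r = 0.5, power with 25 per group is 53%.
- Change score: 62.8 × 2(1 − r) = 25 requires r = 0.80. At r = 0.5, power is 42%.
- Mean of two or three repeated measurements, r from 0.3 to 0.7: 34 to 54 per group.

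**7. All 170 analysed with the partial data used.** Assume 60% retained at three weeks (not in the document) and 30% at six weeks, equal correlation between all visits, and baseline adjustment. For the six-week contrast at SD 7.5, two-sided power is about 56% at r = 0.5, 74% at r = 0.7 and 88% at r = 0.8. One-sided at r = 0.7 it is 83%. At SD 5 and r = 0.5, two-sided, it is about 89%.

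**The case against.** The strongest reply is that the 41% describes an analysis the plan will not run. The plan specifies intention to treat, multiple imputation and repeated measures, which use more than 25 bare six-week scores per group. The hypothesis is directional. The SD of 7.5 is called conservative, and it is the largest population SD a 0-to-15 scale allows (half the scores at each end), so 41% is close to a worst case.

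Much of this stands, and it limits what can be claimed.

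- A reader might infer that the trial is more likely to miss its target effect than to detect it. The document does not support that. It holds for a two-sided, unadjusted test on completers at SD 7.5. It fails one-sided (54%), at SD 5 (74% or 83%), and in the assumed all-170 analysis (56% or more at correlations of 0.5 and above).
- A reader might also infer that power stays below 80% however the data are analysed. It does not. In the same assumed analysis it reaches 88% at a correlation of 0.8, or 83% one-sided at 0.7.

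What the reply does not do is restore the printed result. The section adopts 7.5, and SD 5 does not give 25 either. No correlation is stated, and the sizing counts completers rather than relying on imputation. Complete data on all 85 per group would give 90% power, but with 70% missing at six weeks imputation cannot recover that information.

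One ambiguity cuts the other way. The 3.75 is called a reduction, not a difference between groups. If it is the change within the therapy arm and controls also improve, the true contrast is smaller and power is lower than shown.

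**Conclusion.** Wrong as written. Reading 3.75 as a between-group difference, with SD 7.5, alpha .05 and 80% power, a two-group comparison needs 64 completers per group two-sided or 51 one-sided. The stated 25 is smaller by a factor of about 2.6 or 2.0 (64/25, 51/25).

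The conclusion is that the stated assumptions do not support the stated power. It is not that the trial cannot reach 80% under any assumptions. The shortfall is large at the adopted SD and modest at the historical one: 74% two-sided, while one-sided at SD 5 the 25 would exceed 80%. The arithmetic is certain. The true SD, the between-visit correlation and the origin of the 25 are unknown from the document.

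**What to change.** Correct the sample-size paragraph so that it:

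- says whether 3.75 points is a between-group difference or a within-arm change;
- names the test, its sidedness and any assumed between-visit correlation, with its justification;
- gives the requirement that follows, which is 64 completers per group for d = 0.50 two-sided without adjustment;
- states that 170 recruits with 70% loss yield about 25 completers per group, with about 41% power for 3.75 points at SD 7.5 and about 74% at SD 5 (two-sided), or 80% power only for d of about 0.81.

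If 170 stays, remove the claim of 80% power for 3.75 points and commit to reporting the SDS effect with its confidence interval, alongside the Cohen's d already planned.

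The cost is one rewritten paragraph and a less favourable stated power. The restatement itself needs no extra participants. Keeping 80% power on the stated inputs without adjustment would instead mean recruiting about 427 (two-sided) or 340 (one-sided).

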During the online implementation of the consumption diary of the Snow Control therapy group, we considered asking pilot participants to note the number of cocaine lines consumed. The pilot tests showed that although this includes some numeracy skills, pilot participants did not feel disturbed to note their consumption in grams of cocaine consumed per day. However, because the well-established SDS is utilised as the main outcome and the CCQ-B as a secondary instrument with a randomised control group, we do not expect much influence of purity and quality of the cocaine consumed or the methods of consumption to interfere with the potential outcome differences.

Finally, a potential problem for this trial is the expected high number of lost participants at the end of and at follow up of the online therapy, which will likely be even higher in the control intervention. We will address this issue in three ways. 1) All participants must invest approximately 30 minutes for the baseline assessment, which will select rather motivated participants and prevent the participation of un-motivated participants. 2) Participation at 6 months follow up assessment will be compensated by a 40 Euro incentive (an online voucher or an online charitable donation). 3) All missing values in the final data set will be multiple-imputed, a promising approach that, as shown by our Dutch colleagues, has become increasingly important in e-health research [34].

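### One 70% loss rate is used to size both arms, although the protocol expects worse retention in the control arm; the 25 control completers are therefore not expected, at a small cost in power

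*Protocol article*

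**What the plan says.** In the protocol article, the section Estimation of the Expected Effect Sizes and Sample Size sets the required number: "This results in a total sample of 25 participants in each group (α = .05, 1-β = 0.8". The loss allowance follows: "According to the pilot study, we expect 70% of the participants to quit the study before completion at six weeks". The section then concludes: "We thus aim to recruit a total of 170 participants at baseline". It gives no rate by arm.

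Two other sections expect the arms to differ. Hypotheses states: "We also expect the participants in the therapy group to show significantly higher retention". The Discussion names heavy loss at the end of therapy and at follow-up as a potential problem, and adds of that loss: "which will likely be even higher in the control intervention". Neither section says how large the difference would be.

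**The concern.** The required number is stated per group, and the power claim rests on both groups reaching it. A common loss rate delivers that number with almost nothing to spare, so any excess loss in the control arm takes that arm below it. The protocol predicts such an excess in one section and makes it a hypothesis in another, yet the sizing makes no allowance for it.

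At stake is a stated control-arm size that the design is not expected to deliver, and a power figure quoted for equal groups when unequal groups are anticipated.

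**Working it through.** **Inputs.** From the sample-size section: 25 per group, 70% loss by six weeks, 170 recruits, a difference of 3.75 points, SD 7.5, α = .05 and power 0.8. Assumed: 1:1 allocation (85 per arm), because the ratio is not stated, and a two-sided test, because sidedness is not stated.

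**1. The plan's own figure.** Total = 2 × 25 / (1 − 0.70) = 50 / 0.30 = 167, rounded up to 170. In reverse, 170 × 0.30 / 2 = 25.5 expected completers per arm. The figure reproduces with a common 70% rate.

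**2. Where the control arm drops below 25.** 1 − 25/85 = 70.6%. Any control loss above that gives fewer than 25 in expectation. The binomial probability of at least 25 completers among 85 is:

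| Control loss | Expected completers | P(at least 25) |
|---|---|---|
| 70% | 25.5 | 0.59 |
| 75% | 21.3 | 0.21 |
| 77% | 19.6 | 0.10 |
| 80% | 17.0 | 0.02 |

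**3. How large a gap the retention hypothesis implies.** The protocol gives no control rate. As a benchmark, take the smallest difference that an uncorrected chi-squared test on 85 v 85 would call significant.
- 70% as the rate over both arms (51 completers in all): 32 v 19 gives p = 0.030; 31 v 20 gives p = 0.066. The control arm then misses 25 by six.
- 70% as the therapy-arm rate (about 26 completers): 26 v 15 gives p = 0.049; 26 v 16 gives p = 0.075. Fifteen of 85 is a control loss of about 82%.

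**4. Effect on power.** The model is a two-sample t-test on completers (noncentral t), with noncentrality d × √(n₁n₂/(n₁+n₂)). Two values of d are shown. d = 0.81 is solved so that 25 v 25 gives 80%; it isolates the cost of imbalance and is not the trial's stated effect. d = 3.75/7.5 = 0.50 is the protocol's own.

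| Reading of the 70% | Therapy v control | Power, d = 0.81 | Power, d = 0.50 |
|---|---|---|---|
| Stated plan | 25 v 25 | 80% | 41% |
| Both arms pooled, smallest significant gap | 32 v 19 | 78% | 39% |
| Both arms pooled, 60%/80% loss | 34 v 17 | 76% | 38% |
| Therapy arm only, control 75% | 26 v 21 | 77% | 39% |
| Therapy arm only, control 80% | 26 v 17 | 72% | 35% |
| Therapy arm only, control 82% | 26 v 15 | 68% | 32% |

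On the pooled reading the cost is small because each completer lost from control is matched by one gained in therapy. The total stays at 51, and only the imbalance reduces power.

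**The case against.** The strongest reply is that this barely matters. The sample-size section applies its 70% to the participants as a whole, so it is most naturally a pooled rate. On that reading the total number of completers is unaffected and power moves by about two to four points. That stands, and it sets the size of the point.

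A reader might infer that 70% is the therapy-arm rate, since the Discussion mentions pilot participants trying the consumption diary, which belongs to the therapy tool only. The larger power losses depend on this. The document does not say that the pilot lacked a control tool or that the diary was all it tested, and the pilot's results are not shown, so the inference is not secured.

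A reader might also conclude that the sizing and the retention hypothesis cannot both be true. That goes too far. The Discussion speaks of likelihood and gives no amount, and an overall planning rate can coexist with an expected direction of difference between arms. The shortfall is one of expectation: even at 75% control loss there is about a one-in-five chance of 25 control completers.

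The power model is also simpler than the planned analysis. Data Analysis specifies intention to treat, multiple imputation and repeated measures ANOVA, and logistic regression for retention. The percentages above are therefore guides, not the power of the trial's actual test. This does not remove the point, because the protocol itself sizes on completers and imputation does not supply unobserved control outcomes. The Discussion's three responses to attrition (the effort of the baseline assessment, the six-month incentive and imputation) apply to both arms alike and leave the sizing unchanged.

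**Conclusion.** The point holds as an inconsistency of minor size between planning assumptions. The step from 25 per group to 170 is arithmetically sound for a common 70% loss. The common rate, however, does not fit the protocol's own expectation of worse control retention, and with half a participant to spare the control arm is expected to miss 25 once its loss passes 70.6%. This is so whether 70% is the pooled or the therapy-arm rate; it would fail only if 70% were meant as the control rate, which the section does not say.

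On the plain, pooled reading power drops from 80% to about 78% at 32 v 19, or about 76% at 34 v 17. On the therapy-arm reading it drops to about 77% to 68% for assumed control losses of 75% to 82%. These figures assume 1:1 allocation, a two-sided completer t-test and the effect at which 25 v 25 gives 80%.

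Whether 25 per group follows from 3.75 points and SD 7.5 is a separate question. The 41% at 25 v 25 in the d = 0.50 column belongs to that question; only the further decline down the column belongs here.

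**What to change.** In the sample-size section:
- Say whether the 70% describes both arms together or one of them.
- State a planning loss for each arm that agrees with Hypotheses and the Discussion, or a range, since the document gives no control rate. The sponsor should supply these figures; the rates used above are illustrations.
- Replace the claim of 25 per group at 80% power with the expected completers per arm from 170 recruits, and the power at those unequal numbers. Compute that power from the protocol's own effect and SD, not from an effect solved back from 25 per group.

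The cost is one rewritten and recalculated paragraph, with no extra participants or procedures. The downside is a slightly less favourable stated control count and power. Recalculating from the stated effect and SD will also bring the separate question about 25 per group into view, so the two are best settled together.
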